### Outcomes

The primary outcome is the number of repetitions necessary to reach the predefined proficiency level for procedure B. The secondary outcome is the total effective training time on the simulator for procedure B (in minutes). Exploratory outcomes are the cognitive load and parameters for movements, and time after the first attempt on procedure B. The cognitive load is measured using the Subjective Mental Effort Question (SMEQ), which is a cognitive workload questionnaire designed to allow individuals to rate the amount of effort invested during a task [12]. The questionnaire consists of a scale of 0 to 150 points, with nine scale markers with verbal statements ranging from ‘not at all hard to do’ to ‘tremendously hard to do’. The SMEQ has been previously been published and used in combination with simulator training [13, 14]. The SMEQ is filled out after the first attempt on procedure B. The performance parameters for movement (total path length for both right and left hand and total angular path for right and left hand) and time for the first attempt on procedure B are compared to assess the improvement in motor skills.

### Ethical considerations

The trial complies with the Helsinki Declaration on biomedical research and has been submitted to the Regional Scientific Ethics Committee, which found that in accordance with Danish regulations, ethical approval is not required for carrying out the trial (H-4-2013-FSP). The trial is registered at Clinicaltrials.gov (NCT02069951). The trial complies with the Consolidated Standards of Reporting Trials (CONSORT) statement for randomised trials (Figure 1) [15]. All participants receive verbal and written information on the trial before inclusion; participation is voluntary and participants do not receive any gifts or monetary compensation. All participants can withdraw from the trial at any time with no consequences to their future studies; participants are asked about their reasons for withdrawal but are not obliged to answer. All data is kept confidential and published anonymously.

### Sample size determination

Based on a previous study we expect the control group to take approximately 30 repetitions to reach the proficiency level, with a standard deviation of 15 [10]. A minimal difference of 10 repetitions between the two groups is deemed clinically relevant, meaning that the intervention group is expected to take approximately 20 repetitions to reach proficiency. The standard deviation is assumed to be equal in both groups. With alpha set to 0.05 and beta to 0.10 we need 48 participants in each group, totalling 96 participants.

### Statistical analysis

Data will be analysed using SPSS (Chicago IL, version 20.0), SAS statistical software (SAS Institute Inc., Cary NC, version 9.4) and the statistical software package R (version 3.0.3). A two-sided significance level of 0.05 will be used. The primary and secondary outcomes will be compared using the normal linear multivariable model, adjusting for the two stratification variables. If the assumptions of normality and homogeneity of variance are not sufficiently fulfilled, the outcome data will be transformed. If the assumptions cannot be met by transformation either robust regression, weighted least squares, or bootstrap methods will be applied. If none of these methods seem to give an adequate description of the data, the intervention and control group will be compared using the van Elteren test, and a non-parametric estimate of the confidence interval of the intervention effect will be obtained by bootstrapping [16, 17]. The p-values obtained for secondary and exploratory outcomes will be adjusted for multiplicity using the Benjamin-Hochberg procedure [18].

### Missing data

All analyses are performed according to the intention-to-treat principle. In case of less than 5 percent missing data for the randomised participants for primary and secondary outcome, a complete case analysis will be performed. In case of more than 5 percent missing data, a sensitivity analysis will be performed using a best-worst and worst-case scenario imputation. If these analyses allow for the same conclusion as the complete case analysis, the complete case analysis will be reported. If the best-worst and worst-best case analyses result in a different conclusion than the complete case analysis, multiple imputations will be performed. The multiple imputations will be based on the fully observed variables (that is, sex, intervention, SMEQ-score).

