### Intervention

Participants are invited to participate in an introductory meeting in which information on the trial is given. All participants are informed verbally and in writing by the principal investigator before giving written informed consent. Participants can book three-hour training sessions through an online booking system; only one training session per day is permitted. Training sessions take place at the surgical skills centre at Rigshospitalet, University of Copenhagen. At the first training session, the participants are introduced to the simulator equipment by the principal investigator, and instructed on how to use it. The principal investigator supervises all training sessions and observes that the participants use both correct operating technique and handle instruments correctly. Participants start by practicing six basic skills tasks for isolated skills until they reach a predefined proficiency level for all tasks. The basic skills tasks do not have to be passed in any specific order. After each attempt, the simulator shows the participants automated feedback on each of the different measured parameters. Further more, the principal investigator provides feedback on request. The performance parameters and the predefined proficiency levels for each basic skill modules are listed in Table 1. Upon reaching proficiency for all tasks, the participants are randomised. Those randomised to the intervention group practice two procedures on the simulator to a predefined proficiency level: a laparoscopic appendectomy performed using endoloop technique (procedure A) and followed by a laparoscopic salpingectomy due to an ectopic pregnancy (procedure B). The control group only practices procedure B, Figure 1. The performance parameters and requirements for the predefined proficiency levels for procedures A and B are listed in Table 2. When practicing the two procedural modules, instructor feedback is provided after the first and tenth repetition [10]. The feedback is standardised and focuses on correct technique, instrument handling, and use of diathermy. For both the basic skills modules and the procedural modules, written instructions and video examples of the tasks are available for the participants and can be used at their own discretion. The predefined proficiency level for each module is reached when all of the requirements for the performance parameters is met simultaneously. This has to be archived for two attempts within five consecutive repetitions. The predefined proficiency levels are based on previous studies by the research group [1, 11]. Each participant is expected to use between six and twelve hours within a period of two months to complete the training program.

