### Randomisation

Copenhagen Trial Unit is responsible for a central computerised 1:1 randomisation. The allocation sequence is computer-generated, with a varying block size kept concealed from the investigator. A web-based response system is used to allocate participants after they have completed the basic skills modules (see Intervention). The stratification variables are sex (male/female) and training time to reach proficiency for all basic tasks (less than or equal to two hours/more than two hours).

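### The multiple-imputation list relies on an SMEQ score that early leavers lack and omits basic-skills time, which everyone has and the analysis model uses

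*Protocol article*

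**What the plan says.** The Missing data section of the protocol article sets three steps under intention to treat. Below 5 percent missing data, a complete-case analysis is done. Above 5 percent, best-case and worst-case imputations are added. If these change the conclusion, multiple imputation follows, and its model is specified: "The multiple imputations will be based on the fully observed variables (that is, sex, intervention, SMEQ-score".

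Four other places bear on that list:

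- Outcomes, on the timing of the questionnaire: "The SMEQ is filled out after the first attempt on procedure B".
- Intervention, on the timing of randomisation: "Upon reaching proficiency for all tasks, the participants are randomised". After that, "Those randomised to the intervention group practice two procedures on the simulator to a predefined proficiency level", the appendectomy (A) and then the salpingectomy (B), while "The control group only practices procedure B, Figure 1".
- Randomisation: "The stratification variables are sex (male/female) and training time to reach proficiency for all basic tasks", the latter split at two hours.
- Statistical analysis: the primary and secondary outcomes are compared with the "normal linear multivariable model, adjusting for the two stratification variables".

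Ethical considerations allows withdrawal at any time.

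**The concern.** Two things are wrong with the list.

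First, SMEQ is not complete by design. It comes into existence after randomisation, at the first B attempt, and in the intervention arm that attempt comes only after proficiency on A. Whoever leaves before it lacks the outcome and the SMEQ together.

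Second, the list leaves out a variable that is complete. Basic-skills time must be known before a participant can be randomised. The Discussion calls the stratification variables prognostic, and the analysis model conditions on both of them. Imputing the outcome without a covariate that the analysis model uses makes the two models incompatible: imputed values carry no relation between basic-skills time and the outcome.

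At stake is the step that the plan turns to when missing data put the conclusion in doubt. If slow learners are the ones who leave during A, the imputed intervention participants are given values typical of those who stayed, and the intervention looks better than it is.

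**Working it through.** **Plan's own figure.** Difference 10, SD 15, two-sided alpha 0.05, power 0.90 (Sample size determination, Statistical analysis): n per group = 2 × (1.960 + 1.282)² × 15² / 10² = 47.3, so 48 per group and 96 in total. This reproduces. It is not affected by this point.

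**Trigger.** 5 percent of 96 is 4.8, so 5 missing participants start the extreme-case step.

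**What is known when someone leaves:**

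| Time of leaving | Arm | Sex | Basic-skills time | SMEQ | Primary outcome |
|---|---|---|---|---|---|
| During A (intervention only) | yes | yes | yes | no | no |
| After randomisation, before first B attempt (either arm) | yes | yes | yes | no | no |
| During B, after first attempt (either arm) | yes | yes | yes | yes | no |

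In the first two rows the listed model has only arm and sex to work with.

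**Size, by arithmetic.** Assume half of each arm is slow on basic skills, slow and fast differ by g repetitions on B, and intervention participants leave during A with probability p (slow) or q (fast). The slow share among those who stay is (1 − p) / [(1 − p) + (1 − q)]. Imputing from arm and sex gives leavers the mean of those who stay, so the bias in the arm difference is g × (slow share − 0.5). Negative values favour the intervention.

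- g = 8, p = 0.20, q = 0.05: share 0.80/1.75 = 0.457; bias 8 × (−0.043) = −0.34.
- g = 15, p = 0.40, q = 0.05: share 0.60/1.55 = 0.387; bias 15 × (−0.113) = −1.69.
- g = 15, p = 0.50, q = 0.10: share 0.50/1.40 = 0.357; bias 15 × (−0.143) = −2.14.

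Simulation of the same three settings (1,500 runs, N = 96, SD 15, true difference 10) gave −0.33, −1.81 and −2.19 with the listed variables. The planned adjusted complete-case analysis, and imputation with basic-skills time added, were both within about 0.1 of zero. That is within simulation error: 15 × √(2/48) / √1500 = 0.08 per standard error.

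**Size, with a skewed outcome.** Lognormal repetitions with means 30 and 20 and coefficient of variation 0.5; correlation 0.3 or 0.5 between basic-skills time and log repetitions; the slowest 5 or 8 of 48 intervention participants lost during A; a quarter or a half of participants above two hours. True difference 10:

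| Analysis | Estimated difference |
|---|---|
| Multiple imputation, listed variables | 10.6 to 11.5 |
| Multiple imputation, two-category basic-skills time added | 10.0 to 10.8 |
| Multiple imputation, continuous basic-skills time added | 9.8 to 10.1 |
| Planned adjusted complete case | 9.8 to 10.7 |

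**Limit of the remedy.** When dropout depended on ability not captured by basic-skills time (one setting, leaving probabilities 0.40 and 0.05), the bias was about −2.5 with or without that variable.

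The correlation, the gap g, the share above two hours and all dropout rates are assumptions. The article gives none of them.

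**The case against.** The strongest case against is that this is a conditional third step and the effect is modest. Under the assumed mechanism the bias is about 0.6 to 1.5 repetitions in the skewed setting, against a standard error of √(15²/48 + 10²/48) = 2.6 and a target difference of 10. The primary model and the sample size are untouched. The mechanism is severe: the slowest participants leave, and all of them during A. This stands, and it limits the weight of the point.

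The step is not remote once the threshold is passed. If the extreme values are taken as the observed minimum and maximum, which the article does not specify, 5 intervention dropouts changed the conclusion in 73 to 79 percent of simulated trials with a true difference of 10, and 8 dropouts in 96 to 97 percent.

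A reader might infer more than the documents support:

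- *That imputation fails for these participants.* It does not. A missing SMEQ can be imputed jointly with the outcome; it then adds no information for them.
- *That only the intervention arm is affected.* Controls can also withdraw between randomisation and their first B attempt, and intervention participants who leave during B do have an SMEQ. The imbalance is one of degree, created by the time spent on A.
- *That imputation merely carries over the bias of the complete-case analysis.* That holds for an unadjusted difference in means. The planned complete-case analysis adjusts for basic-skills time and is the less biased of the two.
- *That basic-skills time is the main predictor of the outcome.* The article calls the stratifiers prognostic and says no more.

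It could also be said that the bracketed variables are only examples. The wording introduces them as the definition of the set, so the list reads as closed.

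**Conclusion.** The point holds in this form. The article treats SMEQ as complete although its own schedule makes it missing for anyone who leaves before a first B attempt, and it omits a stratification variable that is always known and is in the analysis model. If dropout in the intervention arm depends on basic-skills time, with slower learners leaving, following the rule as written is more biased in favour of the intervention than the planned adjusted complete-case analysis that it is meant to check: about 10.6 to 11.5 against 9.8 to 10.7 for a true difference of 10. The size depends on assumed correlations and dropout; the contradiction and the omission do not.

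This should be fixed, but it does not threaten the trial. It matters only with 5 or more missing participants and extreme-case analyses that alter the conclusion.

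**What to change.** Replace the bracketed list. Impute the outcome from arm, sex and basic-skills training time. The continuous time is preferable, because the two-hour split recovers only part of the loss (10.0 to 10.8, against 9.8 to 10.1). No longer describe SMEQ as complete; keep it as an auxiliary variable, imputed jointly with the outcome where it is missing.

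This does not deal with dropout driven by unobserved ability, so a sensitivity analysis for that case is a sensible addition. Imputing on the log scale, adding first-attempt movement measures, and using the B repetitions already completed as a lower bound are optional refinements.

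The cost is one sentence in the Missing data section. All the variables are already collected, and the change can be made before the randomisation code is broken.

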## Discussion

### Deliberate practice and task specificity

The presented trial design examines the transferability of skills between different procedural modules on a laparoscopic virtual reality simulator. A previous trial has found that training a basic skill is not an effective strategy for learning a more complex laparoscopic task [6], though most surgical training programs use only isolated or basic skills training [5, 19, 20]. Limited research has investigated which tasks and technical skills should be included in comprehensive minimally invasive surgical curricula [2]. Previous studies have focused on the importance of fidelity for transfer to a clinical setting or transferability between basic and more complex tasks. So far, no studies have examined the transferability between two complex tasks in laparoscopic training; thus, it is unclear whether it is necessary to practice more than one procedural module on a simulator. It is possible that the cognitive aspects of procedural training like instrument coordination, procedural planning, and error recognition could be taught using procedural modules that are different from the procedure that the trainees are supposed to perform in clinical practice. This concept is known as *positive transfer*, in which a previously practiced skill positively influences the acquisition of a new skill. The transfer effect can be caused by either similarities in the cognitive processes used to perform the skill or because the two skills contain many identical elements [21]. According to the specificity of practice hypothesis and Ericsson’s framework for deliberate practice the use of task specific training is important [21, 22]. This includes using both task-specific performance goals and a training setup resembling where the practiced skills is going to be used [23]. This is consistent with two randomised trials’ findings that using a model with higher functional resemblance may yield a better end result and increase transferability [7, 24, 25]. The same observation has been made in sports; for example, different types of throws exist in badminton and there may be a high degree of specificity when learning a specific skill or type of movement [21, 26, 27]. In contrast, results from a recent randomised trial found that practice using simple basic skills compared with a nephrectomy module gave better results when performing a VATS lobectomy in a simulated setting [9]. This is surprising, since the nephrectomy module is more similar to a VATS lobectomy in terms of task resemblance.

A randomised trial has shown that, compared to no training at all, practicing a laparoscopic cholecystectomy on a virtual reality simulator resulted in improved performance when practicing a laparoscopic nephrectomy in a porcine model [8]. This shows that some degree of skills-transfer is seen between different laparoscopic procedures. Furthermore, previous trials have focused on examining the effect in a single-test setting, not considering the effect on the learning process for reaching proficiency for a skill. Developing procedural modules for virtual reality training is very challenging and time-consuming, and it is therefore essential to determine whether it is necessary to develop training modules for many procedures.

### Cognitive load

Increased cognitive load can negatively influence the learning of a new skill and simulator training can be used the to reduce the cognitive load and help facilitate the learning process [28]. Through practicing a procedure on a simulator, the surgical novice can become familiar with the procedure, learn critical steps and how to avoid possible adverse events. For novices, the cognitive load associated with learning a new procedure gradually decreases with continuous simulator practice [14]. Whether this reduction in cognitive load is generalizable and still present when learning a new procedure is unknown and has not been previously examined.

### Trial strengths and limitations

The strength of the present trial is the use of a trial design that mirrors an actual curriculum, because it incorporates both proficiency-based training and distributed practice [29]. Therefore, the findings can probably be applied to actual training in simulation centres. The use of basic skills training to ensure the same proficiency level before randomisation helps standardise the intervention with the procedural modules because the participants have a similar starting point in terms of basic laparoscopic skills. Additionally, use of the same training equipment minimises the risk of confounding from variations in training conditions.

The trial is designed in order to minimise the risks of systematic errors and the risks of random errors [30–32]. Systematic errors have been sought to be reduced by central randomisation stratified for prognostic factors [30–32]. Blinding is used whenever possible and data is analysed according to the intention-to-treat principle. We are aware that some outcomes are at risk of being assessed with some bias, as they are not possible to blind [30–32].

A limitation is the trial participants are medical students instead of novice surgical residents; however, previous studies have shown that medical students’ performance on the simulator is similar to that of novice surgical residents [10, 11]. There are only approximately 50 first-year residents in surgery and gynaecology in the region every year, and they vary greatly in laparoscopic experience; thus, the trial would not have been feasible with first-year residents. Ideally, the trial should include transfer to the clinical settings using clinical outcomes, but this is not feasible due to the large sample size that is required and the difficulty with finding relevant clinical outcomes [33].

### Trial status

Currently, participants are being included and randomisation is still ongoing. Data collection is expected to end in September of 2014.
